### 4.3. Data Collection

#### 4.3.1. Biological Samples and Laboratory Procedures

At visits V−1 and V1, venous blood samples will be collected after an overnight fast of ≥8 h. Blood tests performed will include FPG, HbA1c, total cholesterol, high-density lipoprotein cholesterol (HDL-c), low-density lipoprotein cholesterol (LDL-c), triglycerides (TG), gamma-glutamyl transferase (GGT), aspartate aminotransferase (AST), platelets, leukocytes, high-sensitivity C-reactive protein (hsCRP), interleukin-1 (IL-1), interleukin-6 (IL-6), interleukin-8 (IL-8), advanced glycation end products (AGEs), adiponectin and leptin. Blood samples will be analysed centrally. The TG-glucose index (TG) will also be calculated [58]. Additionally, the expression of relevant genes indicative of metabolic health previously identified [59,60], as well as selected genes with a key role in the pathogenesis of T2D will be assessed by real-time qPCR in blood cells.

#### 4.3.2. Glycaemic Variability

The continuous blood glucose monitoring system (Dexcom G6, Dexcom Inc., San Diego, CA, USA) [61] will be used to assess glycaemic variability for 14 consecutive days in all samples [62]. The sensor will be placed at V−1 and removed after 14 days. It will be placed again at the beginning of week 14 and removed at V1. The Dexcom G6 sensor will be inserted into the subcutaneous adipose tissue in the lower abdomen (below the umbilicus) [19,63]. To optimise the usefulness of continuous glycaemic monitoring, participants will be asked to keep an electronic diary (e-diary), where they will record the food intake, the timing of intakes and the time they go to sleep and wake up during 14 consecutive days. Mean amplitude of glycaemic excursions and time in range (TIR) will be estimated from the 14-day sensor glucose profiles. Mean amplitude of glycaemic excursions will be calculated by taking the mean of the increases or decreases in blood glucose (from nadirs to peaks or vice versa) when the rising and falling segments exceed the 1 standard deviation blood glucose value over a 24 h measurement period [14].

#### 4.3.3. Accelerometer

To quantify PA, SB and sleep, participants will wear a wrist accelerometer on the non-dominant arm for 14 days, 24 h a day (V−1 and V1) [64], and will complete a sleep log. The device (GENEActiv, ActivInsights Ltd., Kimbolton, UK) is a tri-axial accelerometer that allows the following information to be obtained: sedentary time, light PA, moderate PA, vigorous PA and sleep time [65]. The raw data files will be processed with the R package (R Core Team, Vienna, Austria) using the open-source R package GGIR, version 1.2–5 (cran.rproject.org/web/packages/ggir/index.html, access date: 15 December 2022), which has been validated against the self-calibrated functions [66].

#### 4.3.4. Diet

At visits V−1 and V1, diet quality will be assessed using the validated 17-item MedDiet adherence questionnaire [67]. Each item is scored 1 (adherence) or 0 (non-adherence), so the total score can range from 0 to 17, with 0 indicating no adherence and 17 indicating maximum adherence. Moreover, as explained in the glycaemic variability section, to determine the quality of the diet beyond adherence to the Mediterranean diet, and its effects on glycaemic variability, other questions related to diet will be included in the e-diary about the time of each intake and the type and quantity of food intake during 14 consecutive days at baseline and follow-up.

#### 4.3.5. Physical Activity and Sedentary Behaviour

At visits V−1 and V1, the validated REGICOR PA questionnaire for adults, which measures PA levels over the previous 12 months [68], and the validated SB Nurses’ Health Study (NHS) questionnaire for the Spanish population [69] will be administered. The REGICOR PA questionnaire is a sensitive tool to detect moderate and vigorous PA changes in epidemiological studies. It includes a total of 12 questions divided into three categories: questions on the type and intensity of leisure-time physical exercise (walking, brisk walking, walking in the countryside, gardening and climbing stairs), occupational PA and SB, including time spent sleeping. The average daily energy cost of PA is then calculated and expressed in metabolic equivalents (METs) [70]. The REGICOR PA questionnaire also collects data on the average monthly time spent in light (<4 METs), moderate (4–5.5 METs) and vigorous (≥6 METs) PA. Finally, the number of weekly hours of SB is also recorded [68]. The number of hours spent on SB will be recorded using the NHS questionnaire. The types of activities recorded are watching TV, sitting in front of a computer/screen, sitting during transport as a driver or passenger and total sitting time. The frequency of activities is assessed as times in minutes (<30 min; between 30 and 60 min) or hours (between 1 and 9 or more) on an average day, both on weekdays and weekends separately [69].

#### 4.3.6. Anthropometric Measurements

Height, body weight, BMI, waist circumference (WC) and body composition (bioelectrical impedance; Tanita BC-418; Tanita Corp., Tokyo, Japan [71]), will be obtained at visits V−1 and V1 (except for height, which will be measured only at V−1). All anthropometric measurements will be collected according to the recommendations of the International Standards for the Anthropometric assessment (ISAK) [72]. Furthermore, all measurements will be performed by well-trained technicians or researchers to minimize coefficients of variation. Height will be measured to the mm with a book-foot stadiometer with participants standing barefoot and with the head placed in the Frankfort plane; body weight will be measured to the nearest 0. 1 kg with a Tanita body-fat analyser, which will also measure body composition by bioelectrical impedance; BMI will be calculated using the standard formula (weight (kg)/height (m^2^)); and, using a tape measure, WC will be taken at the narrowest point between the lower costal rib and the iliac crest. During height and weight measurements, participants shall adopt a relaxed standing position, with arms crossed over the chest, feet together on the floor and buttock muscles relaxed; both measurements will be taken twice, and the median value will be considered for statistical analyses.

#### 4.3.7. Blood Pressure

At visits V−1 and V1, consecutive blood pressure measurements will be taken in each arm and recorded. The arm with the highest median blood pressure shall be considered for statistical analysis and subsequent measurements during follow-up shall be taken from this same arm (V1). If the median blood pressures of the two arms are identical, subsequent measurements shall be taken from the non-dominant arm. Blood pressure measurements will be taken at the brachial artery after 5 min of rest in a seated position with a validated oscillometer (Omron M3). For statistical analyses, the mean of two measurements taken 2 min apart will be considered.

#### 4.3.8. Quality of Life and Sleep

Quality of life and sleep quality will be assessed at V−1 and V1, using the following validated questionnaires: The European Quality of Life-5 Dimensions (EuroQol-5D) questionnaire is a widely used measure of self-reported health-related quality of life. The questionnaire is divided into two parts. The first comprises five domains: mobility, personal care, usual activities, pain/discomfort and anxiety/depression. For each domain, participants can indicate the level of problems experienced on a three-point categorical response scale (no problem, some problems or severe problems). From the answers given, a single summary score is created, which indicates the self-reported health status. The second part is a Visual Analogue Scale, which captures the overall health perceived by the participant in a score ranging from 0 (worst imaginable health) to 100 (best imaginable health) [73]. The six-item Medical Outcome Study Son Index (Bocado-Sleep) is the shortened version of the 12-item MIS-Sleep scale [74,75]. It is a validated instrument used to assess the quality and quantity of self-reported sleep during the previous month. It uses a list of six items divided into three different domains: sleep disturbances, daytime sleepiness, sleep adequacy, and awakening with shortness of breath or headache. The items are scored on a six-point scale ranging from all the time to never. For interpretation, the direct scores are transformed into a scale from 0 to 100, with no cut-off points; the higher the score, the greater the intensity of the item assessed.

## 5. Results

### 5.1. Main Dependent Variable

The primary outcome variable is the change in MAGE at 15 weeks of follow-up.

Secondary dependent variables are FGP, TIR, HbA1c, TG, blood pressure, body composition, WC, transcriptomic biomarkers in blood and quality of life.

### 5.2. Main Independent Variable

The main independent variable is the assigned group.

### 5.3. Statistical Analysis

Statistical analyses will be performed using R v3.3.1 and the Stata v17.0 program. *p*-values <0.05 will be deemed statistically significant.

- Descriptive analysis, labelling and data cleaning: Assessment of outliers and extreme values, detection and labelling of missing and/or non-applicable values, and description of the distribution of each of the variables. Normality test and scatter plots.

- Descriptive baseline analysis: Sociodemographic characteristics and MAGE and FPG by the different intervention modalities at each phase.

- Main analysis: This will be different for each of the phases and the main analysis will be performed by intention-to-treat. In the first phase, a comparison of MAGE and FPG between the four modalities will be made, and in the second phase the three frequencies will be compared. The ANOVA (GLM) test will be used adjusting by baseline values for both phases. If the assumptions of normality are not met, the Kruskal–Wallis test will be applied. A further adjustment for baseline characteristics, if necessary, will be performed using GLM to determine the effect of membership in each exercise group on decreasing MAGE and FPG. A similar analysis will be performed for each of the secondary dependent variables (HbA1c, TG, blood pressure, body composition, waist circumference and quality of life). Missing values will be replaced using the multiple imputation model (MICE) [76]. Before starting the analysis, a review of possible outliers and range checks for data values will be performed.

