## Abstract

To assess the efficacy of different modalities and frequencies of physical exercise on glycaemic control in adults with prediabetes. A two-phase, parallel, randomised, controlled clinical trial will be carried out, in 210 participants. In phase 1, 120 participants will be randomized into four arms: (1) aerobic exercise, (2) aerobic exercise combined with resistance, (3) high-intensity intervallic exercise and (4) control group. In phase 2, 90 new participants will be randomized into three arms, using the exercise modality that showed the best glycaemic control in phase 1 in the following manner: (1) frequency of 5 days/week, (2) frequency of 3 days/week and (3) frequency of 2 days/week. The control group (n = 30) will be included in phase 1 to evaluate the effect of any type of intervention versus no intervention. Data collection will be performed at baseline and after 15 weeks of follow up. Sociodemographic data, medication, comorbidity, blood biochemical parameters, blood pressure, anthropometric measurements, body composition, physical activity, sedentary lifestyle, diet, smoking, alcohol consumption, quality of life and sleep questionnaires will be collected. Physical activity, sedentary behaviour and sleep will be further determined with an accelerometer, and continuous glycaemia will be determined with a glycaemic monitor, both during seven days, at two time points. The main dependent variable will be the reduction in the mean amplitude of glycaemic excursions. The impact of these interventions on health will also be evaluated through gene expression analysis in peripheral blood cells. The results of this study will contribute to a better understanding of the mechanisms behind the glucose response to physical exercise in a population with prediabetes as well as improve physical exercise prescriptions for diabetes prevention. Increasing glycaemic control in people with prediabetes through physical exercise offers an opportunity to prevent diabetes and reduce associated comorbidities and health costs.

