### 2.2. Secondary Aim

The secondary aims are to evaluate the effect of different physical exercise modalities and frequencies on the following variables: FPG, glycaemic variability measured continuously (24 h), normalization of glycaemic values (reversal), BMI, body composition (percentage and grams of total fat mass and muscle mass), visceral adipose tissue (VAT) waist circumference, lipid profile, inflammation markers, blood pressure, sleep duration and quality and transcriptomic markers of metabolic health assessed in PBC.

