### 3.3. Sample Size and Randomization

The sample size has been calculated to detect significant differences in MAGE of at least 1.5 mg/dL and considering a standard deviation of 1.4 mg/dL [45] in any of the three modalities and a dropout rate of 20%, so 30 subjects will be needed in each group, with a sample of 180 participants, 90 in each phase. Furthermore, a control group (30 patients) will be added to evaluate the effect of any type of monitored exercise in these patients versus usual clinical practice. Randomization will be carried out by permuted blocks of eight in a 1:1:1:1 ratio and stratified by prognostic factors: gender, age and obesity using the open-source Oxford Minimization and Randomization (OxMaR) program [46].

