Different exercise frequencies per week will be compared using the modality that best controlled blood glucose in phase 1: (1) five sessions/week; (2) three sessions/week and (3) two sessions/week. As mentioned above, all groups in both phases will perform a minimum of 150 min of moderate physical exercise per week or 75 min of vigorous exercise per week, always performed under the supervision of a sports science professional.

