## 6. Discussion

The present study will provide information on the efficacy of a supervised physical exercise intervention to reduce FPG in people at risk of T2D, allowing us to determine which exercise modality, and with what weekly frequency, is the most appropriate for a population of adults with prediabetes. Furthermore, this information will be of great use to the scientific community and the general population to increase knowledge about prediabetes reversion.

The GLYCEX study presents some limitations. First of all, any change in habits implies an effort, and therefore, attendance at the intervention sessions may not be as high as desired (more than 80%), which could make it difficult to analyse the effect of the intervention. However, as the sessions are supervised by a sports professional, with small groups and personalized adaptations, it is expected that the volunteers will have better adherence. Secondly, self-reported questionnaires are often based on participants’ statements, with the biases that this may entail. Nevertheless, this study will use validated questionnaires which will not penalize the quality of the results, as well as other objective measurements, such as bioelectrical impedance, blood tests, continuous glucose monitoring, pulsometers and three-axial accelerometers. Thirdly, evaluating the effect of the intervention under experimental conditions compromises the generalization of results in other conditions. Finally, patient recruitment can be difficult and time-consuming. To avoid this limitation, recruitment through primary care professionals will be combined with posters distributed in strategic locations and social network publicity to recruit volunteers.

A strength of the proposed intervention is the personalized approach, which considers the patient’s preferences, giving a choice between different types of aerobic exercise, in two of the three intervention arms of the first phase.

Finally, the results of our study could contribute to better design strategies for the reversion of prediabetes to normoglycemia. Given the increasing prevalence of prediabetes and T2D and the associated costs, determining interventions that could control glycemia in people with prediabetes could be a useful approach to palliate the actual T2D pandemic.

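### Change in MAGE is the only primary outcome, but the main analysis gives FPG equal standing, and the rule for choosing the Phase 2 modality names no endpoint

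*Protocol article*

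**What the plan says.** **Primary outcome.** Section 5.1 states: "The primary outcome variable is the change in MAGE at 15 weeks of follow-up". The Abstract agrees: "The main dependent variable will be the reduction in the mean amplitude of glycaemic excursions". The main aim (section 2.1) is framed on MAGE alone, and the sample size (section 3.3) uses a MAGE difference and a MAGE standard deviation only.

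**Status of FPG.** It is secondary in two places. Section 2.2 opens its list of secondary aims with "FPG, glycaemic variability measured continuously (24 h), normalization of glycaemic values (reversal". Section 5.1 reads "Secondary dependent variables are FGP, TIR, HbA1c, TG, blood pressure", where FGP is evidently a misprint for FPG.

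**Main analysis.** Section 5.3, under its main-analysis heading, says "In the first phase, a comparison of MAGE and FPG between the four modalities will be made". It pairs the two variables again in the further adjusted model, and it leaves FPG out of the bracketed list of secondary variables to be analysed similarly. The only significance rule is p < 0.05. No order, split or hierarchy is given.

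**Selection for Phase 2.** Section 4.1.2 compares frequencies "using the modality that best controlled blood glucose in phase 1". The Abstract refers in the same way to the best glycaemic control. Neither names an endpoint.

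**Discussion.** Section 6 describes what the study will inform as the "efficacy of a supervised physical exercise intervention to reduce FPG in people at risk of T2D" and does not mention MAGE in that sentence.

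**The concern.** There are two separate faults.

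1. A reader cannot tell from the text whether the trial has one main endpoint or two. Sections 2 and 5.1 say one; section 5.3 analyses two side by side. With both tested at 0.05 and no order, a significant FPG result beside a null MAGE result could be reported as a main finding.

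2. The choice of modality sets the intervention for all 90 Phase 2 participants. MAGE, FPG, time in range and HbA1c are all collected, and each could be called control of blood glucose. As written, the choice can be made after seeing which measure favours which arm, and there is no rule for the case where the measures disagree. This is a selection and not a hypothesis test, so the fault is the unnamed endpoint and does not concern alpha.

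**Working it through.** **Inputs.** From section 3.3: difference 1.5 mg/dL, SD 1.4 mg/dL, dropout 20%, 30 per group. Evaluable per group: 30 × 0.80 = 24. Planning effect: 1.5/1.4 = 1.07 SD. From section 5.3: alpha 0.05 per test; four groups in Phase 1, three in Phase 2. The MAGE–FPG correlation and the 0.3 and 0.5 SD advantages below are assumptions; the protocol gives none of them, and no FPG effect or SD.

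**The plan's own figure.** n per group = 2 × [(z for alpha + z for power) × SD / difference]², then divided by 0.80. Power is not stated, so it was varied:

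| Two-sided alpha | Power | n evaluable | n after dropout |
|---|---|---|---|
| 0.05 | 80% | 14 | 18 |
| 0.05 | 90% | 19 | 24 |
| 0.05 | 95% | 23 | 29 |
| 0.05/3 | 90% | 24 | 30 |

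The stated 30 can be reached, and every route uses MAGE alone. The sample size is not at fault on this point.

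**Step 1: error if either endpoint counts.** For two independent tests, 1 − (1 − 0.05)² = 0.0975. For correlated endpoints, two four-group F-tests were simulated with 24 per group and no true effect (20,000 runs per setting):

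| Correlation | P(at least one p < 0.05) |
|---|---|
| 0 | 9.7% |
| 0.3 | 9.7% |
| 0.5 | 9.1% |
| 0.7 | 8.4% |
| 0.9 | 7.2% |

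If MAGE alone is the confirmatory test, its error is 5% whatever happens to FPG.

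**Step 2: how often the two endpoints name different winners.** Three active arms with 24 evaluable each. The arm with the largest mean reduction was taken on each endpoint, with one arm truly better by d on both (arm means simulated as normal with variance 1/24, in SD units):

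| d | Correlation 0 | 0.3 | 0.5 |
|---|---|---|---|
| 0.3 SD (assumed) | 40% | 34% | 29% |
| 0.5 SD (assumed) | 14% | 12–13% | 11% |
| 1.07 SD (planning effect) | 0.04% | 0.04% | 0.04% |

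With no true difference the figures are 67%, 55% and 47%, but then a different winner costs nothing on these endpoints.

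**Step 3: what the repair does to power.** With MAGE as the only main test, pairwise power at the planning effect with 24 per group is Φ(1.07 × √(24/2) − 1.96) = 96%, using the normal approximation and the unrounded 1.5/1.4. No participants need to be added.

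**The case against.** **MAGE is clearly primary, so no error is inflated.** The Abstract and sections 2.1, 3.3 and 5.1 all point to MAGE. On that reading its type I error is 5%, and the 9–10% applies only to an either-endpoint rule that the protocol never states. This stands, and it makes the error figure conditional. It does not remove the contradiction, because section 5.3 is where the analysis is fixed and it does not say that MAGE alone is confirmatory.

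**FPG's absence from the secondary list may be a slip.** That list also omits time in range and the transcriptomic markers, which section 5.1 names as secondary. So the omission alone proves little. The two explicit pairings with MAGE carry the point.

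**Disagreement is negligible if the planning effect is real.** True when one modality beats both others by 1.07 SD. That is a large advantage to expect between two supervised exercise programmes, though the documents give no smaller figure, so 0.3 and 0.5 SD remain assumptions.

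**The Discussion sentence is not an endpoint definition.** Agreed. It needs aligning but is weak evidence.

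**Stronger readings that the documents do not support.** A reader might infer that the four-group test will be followed by unadjusted pairwise tests, with much larger family-wise error. Section 5.3 specifies no pairwise tests, and post-hoc methods are commonly left to an analysis plan that is not shown. A reader might also infer that, because the control arm was added "to evaluate the effect of any type of monitored exercise in these patients versus usual clinical practice", pooled exercise versus control must be the first Phase 1 test. That is a trade-off. If all arms share a 0.7 SD effect, the pooled contrast has 84% power against 68% for the omnibus test; if only one arm works, by 1.07 SD, it has 32% against 97%. The baseline-adjusted model also yields group effects from which such contrasts can be drawn.

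**Conclusion.** The point holds as two defects in the printed text.

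- **Status of FPG.** Section 5.3 contradicts sections 2.2 and 5.1. If either endpoint is allowed to carry the main conclusion, the false-positive risk is about 9–10% per phase at correlations of 0 to 0.5 and about 7% at 0.9. If MAGE alone is confirmatory it is 5%. The protocol must say which.
- **Selection rule.** The endpoint is unnamed. The practical risk depends on how far apart the modalities are: 29–40% disagreement at 0.3 SD, 11–14% at 0.5 SD, and about 0.05% or less at 1.07 SD, for correlations of 0 to 0.5 and 24 evaluable per arm.

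The plan is wrong as written on both counts, and both should be settled before Phase 1 results are seen. Afterwards, a data-driven choice of endpoint or modality could not be ruled out. The conclusion does not extend to the sample size, to post-hoc comparisons or to the choice of the omnibus test.

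**What to change.** 1. **Section 5.3:** state that baseline-adjusted change in MAGE at 15 weeks is the only main analysis in each phase. Remove FPG from both pairings and add it to the list of secondary variables.
2. **Section 4.1.2 and the Abstract:** state that the exercise modality with the largest baseline-adjusted reduction in MAGE in Phase 1 is carried forward.
3. **Section 6:** align the sentence on the study's purpose with MAGE as primary and FPG as secondary.

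The cost is wording, and FPG loses its main-analysis status. No participants are added.

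If the investigators do want FPG as a co-primary endpoint, they should declare it, state an alpha split or a fixed order, and give a rule for disagreement in the selection. With 0.025 for each endpoint, MAGE pairwise power at 24 evaluable per group is 92.9%, and 90% power needs 22 evaluable, or 28 per group after dropout, which is within the planned 30. Power for FPG could not be checked without an FPG effect and SD, which the protocol does not give.

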1)Aerobic Training intervention (AT): Perform 50 min/day, 3 days/week, totalling 150 min/week [34,51] at moderate intensity, as recommended by WHO [26], in a range of 65–75% HRMax. Because any form of aerobic exercise involving large muscle groups and causing sustained increases in HR is likely to be beneficial [52], the type of aerobic exercise will be agreed on with each group of patients, varying from four to eight people. There will be a choice of exercises and participants will be able to choose a combination of up to two different exercises. The participants’ choice of the type of activity to be performed is expected to encourage greater adherence. The range of exercises will be brisk walking or running, swimming and/or aerobic dancing.2)Aerobic Training plus Resistance Training intervention (AT+RT): Perform 50 min/day, 3 days/week, starting with 50% of 1-repetition maximum (1-RM) and follow a progression of increasing loads up to 75% of 1-RM for optimal gains in strength and insulin action [51]. In each session, between five and ten exercises will be worked on, performing 10–15 repetitions, and progressing to 8–10 lifting as the weight increases, involving the major muscle groups from the core, lower body and upper body [53,54]. In all sessions there will be a 3 min warm-up at the beginning of the session and a 2 min cool-down at the end of the session [34].3)High Intensity Interval Training intervention (HIIT): To be considered high intensity, the heart rate needs to be above ≥85% [19,34,55]. Perform 25 min/day, 3 days/week, totalling 75 min/week [34,51] at a vigorous intensity, as recommended by WHO [26]. Starting with four intervals lasting 1 min keeping in a range of 85–90% HRMax, separated by 1 min of low intensity activity (no static) (4 × 1 min intervals), a progression will be followed by increasing the number of circuits, up to ten (10 × 1 min intervals) [19,55,56]. In all sessions there will be a 3 min warm-up at the beginning of the session and a 2 min cool-down at the end of the session [19,34,55,56]. Although the target population is a sedentary population, we expect the HIIT approach, despite being high intensity, to be well received, due to its growing popularity, as demonstrated by a study in which 62% of inactive participants preferred HIIT to other types of exercise [57].4)Participants in the control group will receive written standard PA recommendations in this phase.

#### 4.1.2. Phase 2

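### The main model fixes only the baseline value as a covariate and leaves the stratification factors (sex, age, obesity) to an undefined condition; training groups are also not modelled

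*Protocol article*

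**What the plan says.** - **Outcome.** Section 5.1: "The primary outcome variable is the change in MAGE at 15 weeks of follow-up".
- **Main model.** Section 5.3 specifies an intention-to-treat ANOVA (GLM) adjusted for baseline values in both phases, with Kruskal–Wallis if normality fails. The same item continues: "A further adjustment for baseline characteristics, if necessary, will be performed using GLM". It does not say which characteristics are meant or what would make adjustment necessary.
- **Randomisation.** Section 3.3: allocation is "stratified by prognostic factors: gender, age and obesity". Section 4.2.1 repeats the three factors and applies the procedure to both phases.
- **Delivery of exercise.** For the aerobic training (AT) arm, section 4.1.1 says that "the type of aerobic exercise will be agreed on with each group of patients, varying from four to eight people". The Discussion describes supervised sessions generally, "with small groups and personalized adaptations". No group size is given for the combined arm, the high-intensity interval arm or phase 2. Controls receive written advice only.
- **Training groups in the analysis.** Section 5.3 has no term for them, and nothing in the conditional clause would cover them.

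**The concern.** The design creates two structures that the stated model does not carry.

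The first is stratification. Balancing on prognostic factors reduces the true variance of the arm comparison. A model without those factors does not see the reduction, so it reports standard errors that are too large and gives away precision. The conditional clause does not settle the matter. It sits inside the main-analysis item and addresses the same question, the effect of group on MAGE. Whoever decides that adjustment is necessary, perhaps after seeing a baseline table, therefore also chooses the model.

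The second is shared training. People who train together, and in the AT arm choose the activity together, may have more similar outcomes than people who do not. A model that treats them as independent then reports standard errors that are too small. This matters because phase 1 picks the modality carried into phase 2.

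**Working it through.** **Inputs from the article.** Difference 1.5 mg/dL, SD 1.4 mg/dL, 20% dropout and 30 per group (section 3.3); significance at 0.05 (section 5.3, two-sided assumed); AT groups of four to eight (section 4.1.1). Completers per arm: 30 × 0.8 = 24.

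**Inputs not in the article (assumed).** R², the share of outcome variance beyond baseline explained by sex, age and obesity: 0.10–0.20, with 0 as the no-effect case. Intraclass correlation (ICC) within training groups: 0.01–0.10.

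**1. The plan's own figure.** Power is not stated, so 30 per group has no unique derivation. Using n = 2(z₀.₉₇₅ + z_power)²(1.4/1.5)², divided by 0.8:

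| Power | n evaluable | n with dropout |
|---|---|---|
| 80% | 14 | 18 |
| 90% | 19 | 24 |
| 95% | 23 | 29 |

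A Bonferroni correction for three comparisons at 90% power gives 24, hence 30. The figure is attainable and is not shown to be wrong. With 24 completers per arm, power for one unadjusted comparison is 96%.

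**2. Stratification factors left out.** Reduction in standard error from adjustment = 1 − √(1 − R²):
- R² = 0.10: 1 − √0.90 = 5.1%
- R² = 0.20: 1 − √0.80 = 10.6%

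A null simulation of the four-arm phase 1 analysis used 4,000 runs per scenario, 24 completers per arm, eight exactly balanced strata and a baseline–outcome correlation of 0.5 (assumed). With the factors omitted and no clustering:

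| R² | Model SE / true SE | F-test type I error |
|---|---|---|
| 0 | about 1.00 | 0.048 |
| 0.10 | 1.08 | 0.035 |
| 0.20 | 1.14 | 0.019 |

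Adding the factors brings the error rate back to about 0.05.

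**3. Training groups left out.** Design effect DE = 1 + (m − 1) × ICC, for group size m:
- Smallest: 1 + 3 × 0.01 = 1.03, so 24 completers act as 24/1.03 = 23.3
- Largest: 1 + 7 × 0.10 = 1.70, so 24 completers act as 24/1.70 = 14.1

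For a comparison of two grouped arms, the true two-sided error is 2[1 − Φ(1.96/√DE)]. This gives 0.080 at DE 1.25 (m = 6, ICC 0.05) and 0.110 at DE 1.50 (m = 6, ICC 0.10). Against the ungrouped control the variance factor is (DE + 1)/2, so the standard-error ratio is 1.06 rather than 1.12 at DE 1.25, and 1.12 rather than 1.22 at DE 1.50.

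In the simulation, with all three exercise arms grouped, the control ungrouped and R² = 0, the F-test error was:

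| Group size | ICC 0.01 | ICC 0.05 | ICC 0.10 |
|---|---|---|---|
| 4 | 0.055 | 0.073 | 0.092 |
| 8 | 0.058 | 0.101 | 0.166 |

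Power for one comparison of two grouped arms runs from 95.5% (m = 4, ICC 0.01) to 81% (m = 8, ICC 0.10).

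**4. Both left out, groups of six.** F-test error:

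| R² | ICC 0.01 | ICC 0.05 | ICC 0.10 |
|---|---|---|---|
| 0.10 | 0.035 | 0.072 | 0.097 |
| 0.20 | 0.020 | 0.039 | 0.072 |

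At R² 0.20 and ICC 0.05 the ratio of model to true standard error is 1.02, so the two effects nearly cancel.

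**The case against.** **Scope.** This is a condensed article, and a covariate list is often left to a fuller plan. Sex, age and obesity are baseline characteristics, so the clause could admit them. The wording also calls the adjustment a further one, which can be read as an extra step after a fixed baseline-adjusted analysis. Part of this stands: the factors are not excluded, and a missing list alone would be no finding. But the article does state a rule, and that rule has no trigger and no named variables.

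**Harmless direction.** Omitting the strata makes the test conservative and does not create false positives. That is right; the loss is precision. The simulated effect also assumes exact balance. Section 3.3 gives no cut-points for age or obesity, and incomplete blocks would make the effect smaller. It vanishes if the factors add nothing to baseline MAGE.

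**Training groups.** A reader might infer that all exercise is delivered in groups of four to eight who choose their activity together. The article states that size and that shared choice for AT only. The Discussion speaks of activity choice in two of the three arms, and section 4.1.1 describes prescriptions individualised in real time by heart rate, which may lower the correlation. Nothing shows that group membership is fixed for 15 weeks. These limits stand.

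**Cost of modelling groups.** With 24 completers, groups of eight to four give 24/8 = 3 to 24/4 = 6 groups per arm. A pairwise contrast then has about 2 × (3 − 1) = 4 to 2 × (6 − 1) = 10 between-group degrees of freedom, with a critical t of 2.78 to 2.23 instead of 2.01. The group variance would be poorly estimated. This stands, and it rules out a nested model as the primary analysis.

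**Conclusion.** The concern holds in this form: the main model should name the factors on which randomisation is stratified, and the open condition should go. The gain is about 5–11% in standard errors if the factors explain 10–20% of the variance beyond baseline, and nothing if they explain none. The article gives no value for that share.

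The training-group point is secondary. It rests on an assumed ICC and, outside the AT arm, on an inferred group size.

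It is tempting to conclude that the standard errors are wrong in both directions, or that false positives between modalities are inflated. The documents support neither. A given standard error has one net error. Its sign depends on an R² and an ICC that are not stated, and with both terms omitted the simulated error rate ranges from 0.020 to 0.097 around the nominal 0.05. Nor does this point show the sample size to be wrong.

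**What to change.** 1. In section 5.3, fix one primary model for each phase: MAGE at 15 weeks on arm, baseline MAGE, sex, age (continuous) and obesity or BMI. Because baseline MAGE is in the model, the arm effect is the same whether the outcome is week-15 MAGE or its change.
2. Delete the conditional wording. Any other adjusted analysis should be listed by name as a sensitivity analysis. The Kruskal–Wallis fallback can carry neither covariates nor groups, so it cannot stand in for this model.
3. Record a training-group identifier for each exercise participant during delivery, when it is easiest to capture reliably.
4. Name a sensitivity analysis with a training-group effect in the exercise arms only (a partially nested mixed model with small-sample degrees of freedom). Do not make it the primary model.

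**Cost.** The covariates are already collected. With 24 completers per arm, three added terms take residual degrees of freedom from 96 − 4 − 1 = 91 to 88 in phase 1, and from 72 − 3 − 1 = 68 to 65 in phase 2. The sensitivity analysis needs one identifier per participant and will give wide, imprecise intervals because there are few groups.
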